# Ultrasound-guided *versus* neurostimulation-guided bilateral transperineal pudendal nerve block for analgesia in outpatient haemorrhoid surgery: protocol for a multicentre, randomised, double-blind, non-inferiority trial

**DOI:** 10.1016/j.bjao.2025.100512

**Published:** 2025-12-09

**Keywords:** haemorrhoid surgery, neurostimulation, non-inferiority trial, postoperative analgesia, pudendal nerve block, randomised controlled trial, regional anaesthesia, ultrasound

## Abstract

**Background:**

Haemorrhoid surgery is often associated with severe postoperative pain. Bilateral transperineal pudendal nerve block, performed using anatomical landmarks or nerve stimulation, is effective and currently recommended for postoperative analgesia. However, these blind techniques carry risks such as pudendal artery puncture or rectal injury and are not always routinely performed. The ultrasound-guided transperineal pudendal nerve block has shown promise in paediatric urological surgery, appearing both effective and well tolerated, but has not yet been evaluated in proctological procedures.

**Methods:**

This multicentre, prospective, randomised, double-blind trial aims to compare the analgesic efficacy, adverse effects, and safety of ultrasound-guided *vs* nerve stimulator-guided bilateral transperineal pudendal nerve block in patients undergoing haemorrhoid surgery. The primary endpoint is the maximum pain score (0–10 numerical rating scale) in the post-anaesthesia care unit. Secondary outcomes include length of stay in post-anaesthesia care unit and hospital, quality of recovery score (QoR-15 score), pain and analgesic medication consumption during the first 7 days, and treatment-related adverse effects and safety. A total of 202 patients are required to test non-inferiority, based on a predefined margin of 0.7. The study received ethical approval from the Comité de Protection des Personnes Ouest IV in May 2025.

**Conclusions:**

Recruitment is expected to begin in September 2025. Results will be submitted for peer-reviewed publication and conference presentation.

**Clinical trial registration:**

NCT07015775.

Haemorrhoidectomy is associated with significant postoperative pain, with mean visual analogue scale (VAS) scores ranging from 5 to 6/10 in the immediate postoperative period, often worsening during the first bowel movements.^1^^,^^2^ Effective pain management is therefore essential. Current guidelines^3^^,^^4^ recommend a multimodal analgesic strategy comprising regular administration of a non-steroidal anti-inflammatory drug (NSAID), such as ketoprofen, combined with paracetamol, and rescue opioid analgesia for pain exceeding 4/10. In addition, intraoperative injection of a long-acting local anaesthetic into the ischiorectal fossa—adjacent to the pudendal nerve and its branches—is a key component. This technique, commonly referred to as a pudendal nerve block, has been shown to reduce postoperative pain, decrease opioid consumption, and minimise opioid-related side-effects such as nausea, vomiting, constipation, and delayed gastrointestinal recovery.^5^, ^6^, ^7^

The pudendal nerve, composed of motor, sensory, and autonomic fibres, arises from the sacral roots (S2–S4), exits the pelvis via the greater sciatic notch, loops around the ischial spine, and enters Alcock’s canal after passing between the sacrospinous and sacrotuberous ligaments. It gives rise to several terminal branches innervating the perineum. Sensory blockade of the pudendal nerve can be achieved via two main approaches. The transgluteal route is associated with a high risk of transient sciatic nerve involvement (10–20%),^8^, ^9^, ^10^, ^11^ making it unsuitable for outpatient procedures such as haemorrhoid surgery. The second approach is transperineal, involving injection of local anaesthetic into the ischiorectal fossa, located between the ischium and the anal canal, below the levator ani and coccygeus muscles. This method is currently recommended for postoperative analgesia after haemorrhoid surgery.^3^^,^^4^ It is typically performed using neurostimulation to elicit sphincter contraction and confirm nerve proximity. However, this ‘blind’ technique carries a risk of pudendal artery puncture and possible rectal injury, limiting its routine use. Additionally, obtaining an appropriate motor response with the nerve stimulator can sometimes be challenging. In a large multicentre German study of 770 open haemorrhoidectomies, only 13.5% of patients received a pudendal nerve block.^1^ An ultrasound-guided transperineal pudendal nerve block has been described in paediatric urological surgery,^12^^,^^13^ demonstrating excellent analgesic efficacy and safety, with no sciatic nerve involvement. This technique is used in routine practice by the anaesthesia team at Hôpital Privé Claude Galien. To our knowledge, this is the first randomised controlled trial evaluating the ultrasound-guided transperineal pudendal nerve block for postoperative analgesia in adult haemorrhoid surgery.

The primary objective of this study is to test the non-inferiority of the ultrasound-guided transperineal pudendal nerve block compared with the standard neurostimulation-guided technique for postoperative analgesia in terms of postoperative pain, evaluated by maximal numerical rating scale (NRS) in the post-anaesthesia care unit (PACU). Secondary objectives include comparison of opioid requirements, procedure duration, pain evolution and functional recovery between both techniques. Although adverse events and safety outcomes will be monitored and reported, the study is not powered to detect significant differences in their incidence. This trial aims to generate robust comparative data and evaluate whether the ultrasound-guided technique can safely replace the neurostimulation-guided approach as standard care in proctological surgery.

## Methods

### Patient and public involvement, trial design

A limitation of this study is the absence of a formal Patient and Public Involvement (PPI) process; however, informal feedback from patients regarding their postoperative experience and from members of the public on the clarity of information sheets was taken into account. This is a multicentre, prospective, randomised, double-blind, non-inferiority clinical trial with two parallel groups. Participants will be randomly assigned to receive a bilateral pudendal nerve block either guided by neurostimulation or by ultrasound. This study follows SPIRIT 2025 Checklist. A SPIRIT schedule is provided in Supplementary Materials. A graphical summary of study activities is shown in Figure 1.

**Fig 1 fig1:**
[figure not shown]
Study design.

### Participants, interventions, and outcomes

This trial will be conducted in three private hospitals in France: Hôpital Privé Claude Galien (Quincy-sous-Sénart), Clinique des Côtes du Rhône (Roussillon), and Groupe Hospitalier Diaconesses Croix Saint-Simon (Paris). All centres are equipped with ambulatory surgical facilities and PACUs. The trial will take place in operating theatres and postoperative recovery areas. Participants will be recruited from patients scheduled for outpatient haemorrhoid surgery. Eligibility screening will be performed during preoperative anaesthesia consultations. Study information sheets and oral explanations will be provided at this time, and written informed consent will be obtained before surgery. Randomisation will occur on the day of surgery, and participants will receive either an ultrasound-guided or neurostimulation-guided bilateral pudendal nerve block before the procedure. Recruitment is expected to be completed within 12 months.

Inclusion criteria are adult patients (≥18 yr) undergoing outpatient haemorrhoid surgery under general anaesthesia who provide written informed consent (including pedicular haemorrhoidectomy, stapled haemorrhoidopexy, or haemorrhoidal artery ligation with mucopexy). Exclusion criteria include prior haemorrhoid surgery, contraindication to study medications, spinal anaesthesia, contraindication to the use of a supraglottic airway device, chronic pain requiring opioids, cognitive or language impairments, lack of affiliation with the French health system, legal protection status, pregnancy or inadequate contraception, and participation in another clinical trial.

All procedures will be performed under general anaesthesia using a supraglottic airway device. Anaesthesia will be induced with i.v. propofol (2–4 mg kg^−1^) and sufentanil (0.2 μg kg^−1^), and maintained with sevoflurane (1–3%). Metronidazole (1 g), dexamethasone (8 mg), and droperidol (0.625–1.25 mg) will be administered unless contraindicated. The pudendal nerve block will be performed under general anaesthesia with the patient in the lithotomy position. Patients will be randomly assigned (1:1) to the neurostimulation-guided or ultrasound-guided group.•In the neurostimulation group, after antiseptic preparation, a 22 G, 50 or 80 mm insulated needle (Stimuplex Ultra 360, BBraun, Melsungen, Germany) will be inserted at the midpoint between the anus and the ischial tuberosity, connected to a stimulator (Stimuplex HNS12, BBraun). Electrical stimulation will begin at 2.5 mA with a frequency of 1 Hz. The needle will be advanced to a depth of 4–5 cm until a contraction of the anal sphincter is observed. Once a response is obtained, the current will be reduced to 0.5 mA to confirm appropriate needle placement. If no response is observed, current intensity will be temporarily increased. A strong response at <0.3 mA will prompt repositioning to avoid intraneural injection. After negative aspiration, ropivacaine 15 ml (3.5 mg ml^−1^) will be injected incrementally. The procedure will be repeated contralaterally. If no response is obtained, the block will be performed blindly at a depth of 4 cm.•In the ultrasound group, after antiseptic preparation, a 6 MHz convex probe will be placed transversely on the perineum, between the anus and the ischial tuberosity. The pudendal artery will be identified near the ischial tuberosity. A 22 G, 50 or 80 mm echogenic needle (Ultraplex 360, BBraun, Melsungen, Germany) will be inserted out-of-plane in the area on the medial side of the artery. After negative aspiration, ropivacaine 15 ml (3.5 mg ml^−1^) will be injected slowly. The spread is expected within the ischiorectal fossa. The procedure will then be repeated on the contralateral side.

Block fidelity will be assessed by visualisation of local anaesthetic spread adjacent to the pudendal artery in the ultrasound group, and by the minimal stimulation current eliciting anal sphincter contraction in the neurostimulation group. All investigators were trained and had each performed at least 10 procedures with each technique before trial initiation.

Postoperative analgesic management is standardised, with systematic administration of paracetamol, ketoprofen, and nefopam, and the use of opioid analgesics if pain control is insufficient.

The primary outcome is the maximum pain score in the PACU before opioid administration, assessed using a 0–10 NRS. The NRS was chosen as it is the standardised measure of pain intensity routinely used in the PACUs of all participating centres. Given the variability in length of stay in ambulatory haemorrhoid surgery, more complex or delayed assessments (e.g. repeated measures, early quality of recovery score [QoR-15] ) would carry a higher risk of missing data. The NRS thus provides a simple, robust, and homogenous endpoint across centres. Secondary outcomes include opioid consumption in PACU (converted to i.v. morphine equivalents), nerve block duration, block procedure time, pain scores at rest and during movement at 24 h, 3 and 7 days, total analgesic use over 7 days, timing and pain intensity of first defecation, PACU and hospital stay durations, and adverse events (e.g. sciatic nerve block, haematoma, vascular puncture, rectal injury). Functional recovery will be evaluated with the QoR-15 score on postoperative days 1, 3, and 5.

All adverse events will be documented from randomisation until postoperative day 7 through direct questioning, medical record review, and nursing reports. Each event will be graded (mild, moderate, severe) and assessed for causality (unrelated, possible, probable, definite). Serious adverse events will be reported to the sponsor within 24 h in accordance with French regulations. Based on institutional data (mean pain score 3.4 [2.0]), a non-inferiority margin of 0.7, standard deviation of 2.0, 80% power and one-sided α=0.05, a sample size of 101 patients per group is required. Thus, 202 patients will be enrolled.

### Assignment of interventions

The random allocation sequence will be generated by an independent biostatistician using computer-generated random numbers with randomly permuted block sizes to ensure group balance. No stratification will be applied. Randomisation will be implemented via the electronic case report form (eCRF). Once a participant is enrolled and consented, the investigator enters their data into the eCRF, which automatically assigns them to one of the two intervention groups based on the concealed allocation sequence. The assigned group is then communicated to the designated anaesthesiologist by automated e-mail. This system ensures allocation concealment, as investigators responsible for enrolment and outcome assessment remain blinded to the sequence and block sizes. The allocation sequence is securely stored and inaccessible to trial personnel. Participants and outcome assessors will remain blinded throughout the trial. Only the anaesthesiologist performing the block will be informed of group allocation, and this person must not be involved in enrolment or postoperative outcome assessment (except for block-related procedural data). Unblinding will be permitted only when necessary for immediate clinical management or participant safety. In such cases, the principal investigator may contact the randomisation manager to access the allocation. All unblinding events will be documented, including the reason and requester’s identity.

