Based on preliminary data (mean NRS 3.4 [2.0]), a total of 202 patients (101 per group) is required to test non-inferiority, standard deviation of 2.0, one-sided alpha of 0.05, and 80% power. The non-inferiority margin was set at 0.7 NRS points (20% of the expected mean score), as smaller differences were not clinically relevant and larger ones were considered unacceptable. As the trial follows the intention-to-treat principle, crossovers will be analysed; if patients withdraw consent before surgery, replacements will be recruited to reach 202 participants. A detailed statistical analysis plan will be finalised before database lock. The primary outcome—maximum pain score in the PACU—will be compared using Student’s *t*-test or the Wilcoxon rank-sum test. Secondary outcomes (e.g. opioid use, pain trajectories, QoR-15, length of stay, block duration) will be analysed using appropriate parametric or non-parametric tests. Repeated measures will be assessed via analysis of covariance (ancova), with baseline pain as a covariate. As postoperative pain variability between these procedures was smaller than interindividual variability in our preliminary study, they will be analysed together; however, exploratory subgroup analyses by surgical technique will be conducted if sample sizes allow. Missing data will not be imputed, but patterns and extent of missingness will be described. Sensitivity analyses may be performed if appropriate. Adverse events will be summarised by severity and relationship to the intervention.

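### With no stratification and an unadjusted primary test, variation between the three centres and three operations stays in the error term; prespecified adjustment would recover the lost precision

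*Protocol article*

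**What the plan says.** - **Allocation.** Under Assignment of interventions, the sequence uses "computer-generated random numbers with randomly permuted block sizes to ensure group balance", and the same paragraph states "No stratification will be applied". The ratio is 1:1 and allocation runs automatically through the eCRF.
- **Centres and operations.** Under Participants, interventions, and outcomes: "This trial will be conducted in three private hospitals in France". The eligible operations are listed as "including pedicular haemorrhoidectomy, stapled haemorrhoidopexy, or haemorrhoidal artery ligation with mucopexy".
- **Primary analysis.** Data collection, management, and analysis names Student's t-test or the Wilcoxon rank-sum test for maximum PACU pain. ANCOVA appears only for repeated measures, with baseline pain as covariate. A detailed analysis plan is to be finalised before database lock.
- **Reason for pooling operations.** The same section says that pain varied less between operations than between individuals in preliminary data. It plans exploratory subgroup analyses by technique if numbers allow. It gives no corresponding reason for centre.
- **Sample size.** 101 per group, with a margin of 0.7 and "standard deviation of 2.0, one-sided alpha of 0.05, and 80% power".

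**The concern.** Blocking on a single list keeps the total arm sizes close. It does not keep the arms balanced within a hospital or within an operation. An unadjusted test does not correct such an imbalance afterwards, and it leaves any difference in mean pain between centres or operations in the residual variance.

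The sample size has no slack: 101 per group gives almost exactly 80% power. Precision that could be had for free is therefore worth having, and a result near the margin would be harder to interpret if the arms happened to differ in centre or operation.

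The pooling rationale does not settle this. Being smaller than an interindividual SD of 2.0 still leaves room for a gap between operations larger than the 0.7 margin, and the rationale does not address centres.

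**Working it through.** **1. The plan's own figure.** Inputs: margin 0.7, SD 2.0, one-sided alpha 0.05, power 80% (all stated); true difference 0 (assumed, not stated).

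n per group = 2 × 2.0² × (1.645 + 0.842)² / 0.7² = 100.9, so 101. The stated figure reproduces.

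SE of the difference = 2.0 × √(2/101) = 0.281. Non-inferiority needs an observed difference below 0.7 − 1.645 × 0.281 = 0.24.

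**2. How large chance imbalance can be.** One unstratified list was simulated (202 patients, block sizes 2, 4 and 6 assumed, 5,000 runs).
- In a centre holding a third of the patients (about 67), arm counts differ by 4 at the median and by 13 at the 95th percentile, for example 40 against 27.
- For a stratum holding a third of the patients, its share differs between arms by more than 10 percentage points in about 12% of trials. The 95th percentile is about 13 points.

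The shift in the treatment difference is the imbalance in share times the gap in mean pain between that stratum and the rest (gaps assumed):

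| Gap (NRS points) | Shift at 95th percentile | Share of 0.7 |
|---|---|---|
| 0.5 | 0.06 | 9% |
| 1 | 0.13 | 18% |
| 2 | 0.26 | 37% |

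The percentile is of the absolute imbalance, so an unfavourable shift this large occurs in about 2.5% of trials. These shifts are a component of the 0.281 SE, not an addition to it.

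**3. What adjustment recovers, in closed form.** Assume three equal strata with means −g, 0 and +g, and total SD held at 2.0. Between-stratum variance is 2g²/3; adjustment removes it from the residual. With balanced arms, power = Φ(0.7/SE − 1.645).
- g = 0: SE 0.281, power 80.0%.
- g = 0.5: variance removed 0.167 (4% of 4.0); residual SD √3.833 = 1.958; SE 0.276; power 81.5%.
- g = 1: variance removed 0.667 (17% of 4.0); residual SD √3.333 = 1.826; SE 0.257; power 86.0%.

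**4. The same by simulation** (4,000 runs per scenario), strata 1 point apart:

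| Allocation | Analysis | Power at true difference 0 |
|---|---|---|
| Unstratified | Unadjusted | 81% |
| Stratified | Unadjusted | 81% |
| Unstratified | Adjusted | 85% |
| Stratified | Adjusted | 86% |

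The simulated gain from adjustment is 4 to 5 points. The closed form gives 6; simulation error on a difference of two powers is about √(2 × 0.8 × 0.2/4000) = 0.9 points, so the two agree. At 0.5-point steps all four cells lie between about 80% and 82%.

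**5. Type I error.** With the true difference set at 0.7, rejection rates ran from 4.0% to 5.4% across all scenarios, with Monte Carlo error about 0.3 points. There is no inflation.

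**The case against.** The strongest reply is that unstratified permuted-block allocation of 202 patients is a legitimate design, and that the article contradicts nothing in choosing it. That stands. A reader might infer that the lack of stratification biases the comparison or undermines the non-inferiority conclusion. The documents do not support that: the imbalance is random, already counted in the SE, and leaves type I error at its nominal level.

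A reader might also infer that the hospitals are known to differ in pain scoring, case mix or skill. The text does not show this. It describes the NRS as the routine measure in every participating PACU, standardises postoperative analgesia, and requires each investigator to have done at least 10 procedures with each technique. It does say of one site "This technique is used in routine practice by the anaesthesia team at Hôpital Privé Claude Galien", but it is silent on the other two.

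Third, stratifying alone buys almost nothing: 81% against 81% in the simulation. That also stands, and it is why the recommendation rests on adjustment.

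Finally, the analysis plan is not shown and may already adjust. If so, the point is met. The article nevertheless names an unadjusted test for the primary outcome.

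**Conclusion.** The point holds as a modest, inexpensive improvement in precision, not as an error. Neither the allocation nor the stated primary test uses centre or operation, and the reason given for pooling neither excludes gaps above 0.7 between operations nor covers centres.

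The loss is about 4 to 5 power points if three equal strata lie 1 NRS point apart (so the extremes differ by 2), and almost none at 0.5-point steps. The gaps, stratum shares and block sizes are assumptions, because the article reports none of them. The sample size of 101 per group is unaffected.

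**What to change.** Before database lock, prespecify the primary non-inferiority analysis as a linear model (ANCOVA) of maximum PACU NRS on arm, adjusted for centre and for planned surgical technique as recorded before randomisation. Compare the upper one-sided 95% confidence limit for the arm difference with 0.7. Keep the unadjusted comparison as a sensitivity analysis.

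If enrolment has not started, also stratify the eCRF lists by centre. Ethics and dissemination schedules recruitment from September 2025 and the article appeared in December 2025, so enrolment may be under way; in that case keep the existing list and rely on adjustment.

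The cost is a few degrees of freedom and slightly more analysis work. Stratifying before enrolment would also need the eCRF list reprogrammed, a short amendment, and a few more incomplete blocks.

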### Data collection, management, and analysis

Clinical data will be collected using a secure eCRF developed with ENNOV Clinical® (ENNOV, Paris, France) and hosted on general data protection regulation (GDPR)-compliant servers located in France. Investigators will receive secure credentials and enter data directly into the eCRF. Paper CRFs may be used as backup and transcribed subsequently.

Subjective assessments (e.g. pain scores, QoR-15) will be conducted by the same assessor when possible. All entries, corrections, and validations will be made by investigators or authorised site staff. The eCRF includes automated range and consistency checks to enhance data quality. The study will be monitored by the sponsor or its representative through on-site visits to ensure concordance between source data and CRFs. Data queries will be issued and resolved accordingly. Final quality checks will be conducted in accordance with the statistical analysis plan. Essential documents will be archived for a minimum of 15 yr, as required by French regulations. Data access will be strictly controlled and confidential. Audits or inspections will be allowed in compliance with these standards.

Based on preliminary data (mean NRS 3.4 [2.0]), a total of 202 patients (101 per group) is required to test non-inferiority, standard deviation of 2.0, one-sided alpha of 0.05, and 80% power. The non-inferiority margin was set at 0.7 NRS points (20% of the expected mean score), as smaller differences were not clinically relevant and larger ones were considered unacceptable. As the trial follows the intention-to-treat principle, crossovers will be analysed; if patients withdraw consent before surgery, replacements will be recruited to reach 202 participants. A detailed statistical analysis plan will be finalised before database lock. The primary outcome—maximum pain score in the PACU—will be compared using Student’s *t*-test or the Wilcoxon rank-sum test. Secondary outcomes (e.g. opioid use, pain trajectories, QoR-15, length of stay, block duration) will be analysed using appropriate parametric or non-parametric tests. Repeated measures will be assessed via analysis of covariance (ancova), with baseline pain as a covariate. As postoperative pain variability between these procedures was smaller than interindividual variability in our preliminary study, they will be analysed together; however, exploratory subgroup analyses by surgical technique will be conducted if sample sizes allow. Missing data will not be imputed, but patterns and extent of missingness will be described. Sensitivity analyses may be performed if appropriate. Adverse events will be summarised by severity and relationship to the intervention.

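### The stated primary analysis (t-test or Wilcoxon rank-sum test) is not tied to the 0.7-point non-inferiority margin on which the trial is designed and sized

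*Protocol article*

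**What the plan says.** The aim is clear. The objectives paragraph that closes the introduction of the Protocol article states: "The primary objective of this study is to test the non-inferiority of the ultrasound-guided transperineal pudendal nerve block". The title, abstract and trial design agree.

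The section on data collection, management and analysis gives the margin and where it comes from: "The non-inferiority margin was set at 0.7 NRS points (20% of the expected mean score"). The same paragraph gives the design values, "standard deviation of 2.0, one-sided alpha of 0.05, and 80% power", and the result, "a total of 202 patients (101 per group) is required to test non-inferiority".

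For the analysis itself, the paragraph says only that the primary outcome "will be compared using Student’s *t*-test or the Wilcoxon rank-sum test". It then adds no null hypothesis, confidence interval or rule for concluding non-inferiority. The margin and the one-sided alpha appear only in the sample-size justification. On further detail it says: "A detailed statistical analysis plan will be finalised before database lock".

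**The concern.** A non-inferiority claim rests on rejecting the hypothesis that the new technique is worse by the margin or more. A t-test or rank-sum test, named without further qualification, is usually understood as a test of no difference. Failing to reject that null is not evidence of non-inferiority, and rejecting it in favour of ultrasound is a stricter demand than the trial was sized for. So the named analysis, taken in its usual form, matches neither the objective nor the sample size.

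The rank-sum option adds a second difficulty. The margin is a fraction of the expected mean, so it lives on the scale of mean NRS points. A rank-sum p-value supplies no estimate on that scale. With no criterion for choosing between the two tests, the quantity being compared is also left open. The outcome is a bounded 0–10 score with expected mean 3.4 and SD 2.0, so the non-parametric route is a realistic possibility.

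At stake is the error rate of the trial's main conclusion.

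**Working it through.** **Inputs** (all from the Protocol article): margin 0.7, SD 2.0, one-sided alpha 0.05, power 80%, 101 per group (analysis section, also given in the outcomes section); expected mean 3.4; 1:1 allocation (interventions section). The assumed true difference is not stated; I take it as 0.

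**1. Reproduce the sample size.** n per group = 2 × SD² × (z₀.₉₅ + z₀.₈₀)² / margin² = 2 × 4 × (1.645 + 0.842)² / 0.49 ≈ 100.9, rounded up to 101, so 202 in total. This matches the article exactly. The trial was sized for a margin-based test with a true difference of 0.

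**2. Standard error of the mean difference.** SE = 2.0 × √(2/101) = 0.281.

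**3. What a margin-based test requires.** Non-inferiority needs observed difference + 1.645 × SE < 0.7, that is, an observed difference below 0.700 − 0.463 = 0.237, about 0.24 NRS points (ultrasound minus neurostimulation).

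**4. What a test of no difference would let through if non-significance were taken as non-inferiority.**
- One-sided 5% test for ultrasound being worse: non-significant up to 1.645 × 0.2814 = 0.46.
- Two-sided 5% test: non-significant up to 1.96 × 0.2814 = 0.55.

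Observed differences from 0.24 up to 0.46 or 0.55 would then pass although they fail the margin.

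**5. Probability of passing, by true difference d** (normal approximation). Margin test: Φ((0.7 − d)/SE − 1.645). One-sided non-significance: Φ(1.645 − d/SE). Two-sided non-significance: Φ(1.96 − d/SE) − Φ(−1.96 − d/SE).

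| True difference d | Margin test | One-sided 5% test not significant | Two-sided 5% test not significant |
|---|---|---|---|
| 0 | 80.0% | 95.0% | 95.0% |
| 0.3 | 41.2% | 71.9% | 81.3% |
| 0.5 | 17.5% | 44.8% | 57.3% |
| 0.7 | 5.0% | 20.0% | 29.9% |

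If instead a significant one-sided result in favour of ultrasound were required, success at true equality would be 5%, not 80%.

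**6. Check by simulation** (10,000 trials, normal data, 101 per arm). At d = 0.7, the two-sided test of no difference was non-significant in 30.9% (t-test) and 33.3% (rank-sum). With the null shifted by 0.7, the t-test gave 79.8% power and 5.4% type I error; the rank-sum test gave 77.9% and 5.2%. Both named tests can therefore serve if they are tied to the margin. For the rank-sum test this relies on a pure location shift, which holds by construction in these data but is debatable on a bounded 0–10 scale.

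**The case against.** The strongest reply is that the article never says the null is zero difference. A t-test against a null shifted by 0.7 is a standard non-inferiority test, and a rank-sum test can be shifted in the same way under a location-shift model. The paragraph that names the tests also gives the margin, the one-sided alpha and the intention to test non-inferiority. The article condenses a full protocol (version 5.0) and points to an analysis plan, neither of which is shown, and either may carry the decision rule.

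Much of this stands. It rules out the claim that the named tests cannot answer the objective. It also means that the 20% and 30% figures describe a possible misreading, not the planned rule. The 30% figure needs a two-sided 5% test as well, whereas the only alpha stated is one-sided 0.05.

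What does not stand is that this is merely detail left for later. The article does not stay silent on the primary test: it names one, in a form that usually carries the wrong null for this objective, and pairs it with an alternative that yields no quantity on the margin's scale.

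A reader might also infer that the choice of test will be made after seeing results by arm. The documents do not support that. Database lock is a latest date for the analysis plan. The section on assignment keeps participants and outcome assessors blinded and the allocation sequence inaccessible to trial personnel, and the monitoring section plans no interim analysis.

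**Conclusion.** The point holds as a mismatch of wording at the centre of the trial: design and sample size are margin-based, while the stated primary analysis is not linked to the margin and leaves two tests open without a criterion. If non-significance were read as non-inferiority, the false-claim rate at a true difference of 0.7 would be about 20% to 30% instead of 5%. These figures assume SD 2.0, 101 analysed per group and approximate normality of the mean difference.

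Two stronger readings should be resisted. The article does not show that the investigators intend to infer non-inferiority from a non-significant test. Nor is the sample size wrong: it reproduces, and it gives 80% power and 5% type I error under the margin-based rule. The general warning that a significant small difference need not mean inferiority also has no bite at these values, because a significantly worse result (above 0.46 or 0.55) would already fail the 0.24 threshold.

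**What to change.** Replace the primary-analysis sentence with wording to this effect:

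- The mean difference in maximum PACU NRS, ultrasound minus neurostimulation, will be estimated with its two-sided 90% confidence interval.
- Non-inferiority will be concluded if the upper limit is below 0.7.
- Any non-parametric analysis, for example a Hodges–Lehmann shift estimate with its confidence interval, is a prespecified sensitivity analysis and does not decide the primary conclusion.

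The interval from the t-test already named is sufficient; no more elaborate model is needed. If the analysis plan already contains this rule, the article and the plan need only be made to agree. The cost is a wording change, with no extra patients or data and no change to the 202.
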